### **3.5. Sample size calculation**

Calculation of the number of clinical study subjects: As this study is an investigator-initiated clinical trial, the sample size was determined by referencing existing similar studies and clinical experience..

- 1) Level of significance,  $\alpha=0.05$ (two-tailed test)
- 2) Type II error ( $\beta$ ) is set at 0.2, making the power of the test 80%.
- 3) There is no existing study comparing Korean Chuna therapy and usual care for TMJ-related conditions in Korea. Therefore, based on clinical experience and manual therapy studies in China 1-3), the effect size for comparing the mean differences in pain VAS between the two groups is assumed to be at least medium (effect size = 0.7).
- 4) G\*Power 3.1.7 is used to calculate the sample size.

Assuming an effect size of 0.7, 34 subjects per group (a total of 68 subjects) are required. However, since the main analysis will be performed using ANCOVA, adjusting for baseline outcome values, and assuming a correlation value of 0.3 between baseline and the primary endpoint, the sample size is calculated as  $(1 - 0.3 * 0.3) * 68$ , resulting in 62 subjects. Considering a 30% dropout rate during the study, a total of 80 subjects will be recruited, with 40 subjects per group.

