#### 5.2.2. Allocation concealment and blinding

After providing patients with a thorough explanation of the clinical study, those who meet the inclusion and exclusion criteria and sign the written consent form will be assigned to groups using opaque, sealed envelopes. Since it is not feasible to blind the practitioners and participants in this study, only the assessors will be blinded. Assessor, who do not participate in the procedures and are blinded to group assignments, will conduct assessments in a separate area after the procedures are completed. These evaluations will be performed by clinical research coordinator or residents.

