## 6. Outcomes

### 6.1. Primary outcomes

#### Visual Analogue Scale (VAS) for TMJ pain

VAS will be evaluated on the 1st, 3rd, 5th, and 7th treatment visits (week 1–4) and 5 weeks, 3 months, and 6 months after allocation. The average TMJ pain for the past week will be investigated. The primary endpoint is VAS at 5 weeks after allocation (a week after the last treatment). The far left end of a 100 mm scale line means “no pain” and the far right end means “the worst pain imaginable.” It is the most frequently used way to measure the pain severity. A participant puts a mark on the line, which approximates his/her own pain for the past week. If a participant complains of different pain levels on each TMJ, the more severe side will be recorded.

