#### **6.3.2 General principles of analysis**

- This study analyzes the results of pain intensity scale, functional scale, quality of life, and cost data for patients who meet the inclusion criteria in a randomized controlled trial.
- The primary analysis will use the ITT (Intention-to-Treat) approach, evaluating all subjects who received at least one treatment. Additionally, the PP (Per-Protocol) analysis will be conducted alongside, evaluating only those subjects who completed the clinical study without dropping out. Missing data will be handled primarily through Multiple Imputation, and LOCF (Last Observation Carried Forward) will be used for sensitivity analysis.
- The socio-demographic characteristics and treatment expectancy of the study subjects will be evaluated by group. Continuous variables will be expressed as mean (standard deviation) or median (interquartile range) and compared between the two groups using Student's t-test. Categorical variables will be expressed as frequency (%) and analyzed using the chi-square test or Fisher's exact test.
- The efficacy evaluation variables of this clinical study are the differences in the changes of continuous outcomes (VAS, NRS, MMO, K-BDI-2, JFLS, SF-12, EQ-5D-5L, EQ-VAS) between the two groups from baseline to each time point. ANCOVA (Analysis of Covariance) will be performed with the baseline values of each variable and the covariate factors that show statistical differences between the

treatment groups at baseline as covariates, and the group as a fixed factor. RM ANOVA (Repeated Measures ANOVA) will be conducted to test the differences in trends at each visit.

- To compare the total amount of differences in each outcome within the period (evaluation time point after treatment completion (5 weeks)) and the entire study period (6 months), the areas under the curve (AUC) at each time point after randomization will be calculated and compared using Student's t-test.

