### 1.1 General principles of analysis

- This study analyzes the results of pain intensity scale, functional scale, quality of life, and cost data for patients who meet the inclusion criteria in a randomized controlled trial.
- The primary analysis will use the ITT (Intention-to-Treat) approach, evaluating all subjects who received at least one treatment. Additionally, the PP (Per-Protocol) analysis will be conducted alongside, evaluating only those subjects who completed the clinical study without dropping out. Missing data will be handled primarily through Multiple Imputation, and LOCF (Last Observation Carried Forward) will be used for sensitivity analysis.
- The socio-demographic characteristics and treatment expectancy of the study subjects will be evaluated by group. Continuous variables will be expressed as mean (standard deviation) or median (interquartile range) and compared between the two groups using Student's t-test. Categorical variables will be expressed as frequency (%) and analyzed using the chi-square test or Fisher's exact test.
- The efficacy evaluation variables of this clinical study are the differences in the changes of continuous outcomes (VAS, NRS, MMO, K-BDI-2, JFLS, SF-12, EQ-5D-5L, EQ-VAS) between the two groups from baseline to each time point. ANCOVA (Analysis of Covariance) will be performed with the baseline values of each variable and the covariate factors that show statistical differences between the treatment groups at baseline as covariates, and the group as a fixed factor. RM ANOVA (Repeated Measures ANOVA) will be conducted to test the differences in trends at each visit.
- To compare the total amount of differences in each outcome within the period (evaluation time point after treatment completion (5 weeks)) and the entire study period (6 months), the areas under the curve (AUC) at each time point after randomization will be calculated and compared using Student's t-test.

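### The 5-week and 6-month AUCs are compared by an unadjusted t-test, a valid choice that gives up precision which the baseline values, already collected and already used at each visit, would supply

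*Protocol*

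**What the plan says.** Section 6.3.2 compares each outcome over two periods, "within the period (evaluation time point after treatment completion (5 weeks)) and the entire study period (6 months", and fixes the method: "the areas under the curve (AUC) at each time point after randomization will be calculated and compared using Student's t-test". Section 1.1 of the Statistical Analysis Methods has the same text, ending "will be calculated and compared using Student's t-test". Neither place names a covariate.

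The preceding item in both sections treats the same continuous outcomes differently at each time point: "ANCOVA (Analysis of Covariance) will be performed with the baseline values of each variable". Section 3.5 reduces the sample size on the strength of baseline adjustment, "assuming a correlation value of 0.3 between baseline and the primary endpoint".

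On timing, the Timetable puts allocation at Week 0 and the first VAS in Week 1. Section 6.1 agrees: "VAS will be evaluated on the 1st, 3rd, 5th, and 7th treatment visits (week 1–4", followed by 5 weeks, 3 months and 6 months. It also says "The average TMJ pain for the past week will be investigated". There is no earlier VAS, so the first reading after randomisation also serves as the VAS baseline. For K-BDI-2, JFLS, SF-12, EQ-5D-5L and EQ-VAS, section 6.2 says that the first-visit reading precedes treatment. For VAS no such statement is made, and section 5.2.2 says that assessors "will conduct assessments in a separate area after the procedures are completed".

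**The concern.** An area that starts at the first reading after randomisation includes the baseline value, which treatment cannot have changed. The later readings in the area are correlated with that value as well. A two-sample t-test leaves all of this variation in the error term, although the plan collects the baseline and adjusts for it one item earlier.

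Two things are at stake. The interval for the AUC difference is wider than it need be. And with 40 patients per arm, an ordinary chance imbalance can make the unadjusted AUC and the adjusted Week 5 result point to different sizes of effect for a reason unrelated to treatment. The trial report would then have to explain a discrepancy that its own choice of test produced.

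**Working it through.** **The plan's own figure.** For an effect size of 0.7 the noncentral t gives 33.02, rounded up to 34 per group, 68 in all. The ANCOVA factor gives 68 × (1 − 0.3²) = 61.88, that is 62. Both match section 3.5. That credit concerns the primary endpoint, which does receive ANCOVA.

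**Inputs from the protocol.** VAS at Weeks 1, 2, 3, 4, 5, Month 3 and Month 6 (section 6.1). JFLS at the first treatment visit and a week after the last treatment (section 6.2). Baseline to Week 5 correlation r = 0.3 (section 3.5). 40 per arm.

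**Assumptions, not in the protocol.** Trapezoid rule; Months 3 and 6 placed at Weeks 13 and 26; equal SDs at all visits; r = 0.3 at every later visit; correlation ρ among follow-up readings from 0.3 to 0.8.

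**Formulas.** Divide the area by its length, so the weights sum to 1. Let w be the weight of the first reading and S the sum of squared follow-up weights. In units of the outcome's variance:

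- covariance of area with baseline: c = w + (1 − w)r
- variance of the area: V = w² + 2w(1 − w)r + S + [(1 − w)² − S]ρ
- share explained by baseline: R² = c²/V
- excess width of the unadjusted interval: 1/√(1 − R²) − 1

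**5-week VAS area.** Weights 0.125, 0.25, 0.25, 0.25, 0.125. c = 0.125 + 0.875 × 0.3 = 0.3875. V = 0.2844 + 0.5625ρ.

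**6-month VAS area.** Weights 0.02, 0.04, 0.04, 0.04, 0.18, 0.42, 0.26. c = 0.02 + 0.98 × 0.3 = 0.314. V = 0.2934 + 0.6792ρ.

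**Two-reading 5-week area** (JFLS; also K-BDI-2, SF-12, EQ-5D-5L, EQ-VAS up to Week 5). Weights 0.5, 0.5. c = 0.65. V = 0.25 + 0.25 + 0.5 × 0.3 = 0.65, whatever ρ is.

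| Area | First-reading weight | V (ρ = 0.3 to 0.8) | R² | t-test interval wider by |
|---|---|---|---|---|
| VAS, 5 weeks | 12.5% | 0.453 to 0.734 | 33% to 20% | 22% to 12% |
| VAS, 6 months | 2% | 0.497 to 0.837 | 20% to 12% | 12% to 6.5% |
| Two readings, 5 weeks | 50% | 0.65 | 65% | 69% |

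**First reading left out of the VAS area.** Now c = 0.3. At 5 weeks the weights are 1/6, 1/3, 1/3, 1/6 and V runs from 0.494 to 0.856, so R² = 0.09/V = 18% to about 11%. At 6 months V runs from 0.513 to 0.861, giving nearly the same, 18% to 10%. Dropping the reading therefore does not remove the reason to adjust.

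**Chance imbalance.** A baseline difference of 1 SD carries an expected shift of c in the mean over the period: 0.39 SD at 5 weeks, 0.31 SD at 6 months. The standard error of the area difference at 40 per arm is √(2V/40). For an imbalance of 0.3 SD:

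- 5 weeks: 0.3 × 0.3875 = 0.116, against standard errors of 0.151 to 0.192, that is 0.77 to 0.61 standard errors
- 6 months: 0.3 × 0.314 = 0.094, against 0.158 to 0.205, that is 0.60 to 0.46 standard errors

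The baseline difference itself has standard error √(2/40) = 0.224 SD, so 0.3 SD is 1.34 standard errors. An imbalance at least that large in either direction occurs in about 18% of such trials.

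**Sensitivity to r.** With r = 0.2 and ρ = 0.5, R² is 17% (5 weeks) and 7% (6 months). With r = 0.5 and ρ from 0.5 to 0.7 it is 52% to 44% and 41% to 34%. If correlation decays with time and reaches 0.3 at Week 5, it is 49% and 7%.

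**Power, illustration only.** An effect rising linearly to 0.7 SD at Week 5 averages 0.35 SD over the area. With 40 per arm and ρ from 0.5 to 0.7, power is 54% to 47% by t-test and 67% to 57% by ANCOVA. The protocol sets no power target for the AUC.

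**The case against.** The t-test is not a wrong test. Randomised groups have equal expected baselines, so it is unbiased and its type I error is correct. A reader might infer from the baseline reading inside the area that the comparison is biased; the design does not support that. This part of the objection stands in full.

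The main inference is also protected. The primary endpoint is VAS at 5 weeks and gets ANCOVA, as does every continuous outcome at each time point. The AUC is supplementary and unpowered. A reader might infer that the reduction from 68 to 62 in section 3.5 is undermined; it is not, because that reduction concerns the primary endpoint alone.

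The sizes rest on assumptions. Section 3.5 gives 0.3 for one pair of time points, and nothing in the protocol gives SDs by visit or correlations among follow-up readings. At 6 months the first reading weighs only 2%, and most of the gain there comes from the later readings' assumed correlation with baseline. NRS is taken at every treatment visit, a different schedule, and is not computed here.

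Finally, the first VAS is pre-treatment only by inference. Section 5.2.2 puts assessments after procedures, while the one-week recall points to the time before treatment. Where an area starts may also be left to a statistical analysis plan. But the protocol does fix the test, twice, and the case for the covariate survives if the first reading is excluded.

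**Conclusion.** The point holds as a loss of precision on a supplementary analysis that can be recovered without new data. It is not a bias, and it does not touch the primary result. Under equal SDs, r = 0.3 at all later visits and follow-up correlations of 0.3 to 0.8, the unadjusted test keeps 20% to 33% avoidable variance in the 5-week VAS area, 12% to 20% in the 6-month VAS area and 65% in two-reading 5-week areas.

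No single figure covers all outcomes. A reader might settle on about a quarter, but that fits only the 5-week VAS area with follow-up correlations near 0.5 to 0.7 (26% to 22%). The 6-month gain could be smaller, about 7%, if correlation with baseline fades over time. The direction does not depend on these choices: as long as baseline is appreciably correlated with the area, adjustment gains precision and keeps the AUC analysis in line with the visit-wise one.

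**What to change.** In section 6.3.2 and in section 1.1 of the Statistical Analysis Methods, replace the t-test for the AUC by ANCOVA of the AUC with arm as the factor and that outcome's baseline value as the covariate, for both periods. State which reading serves as the baseline for each outcome and, for VAS, whether it is taken before the first treatment.

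The covariate is the essential part. The first reading may stay in the area or be left out, but leaving it out while keeping the t-test is not enough. The unadjusted comparison can be kept as a descriptive supplement.

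The cost is one sentence in two places, with no new data and no change to the sample size or the primary analysis. It should be settled before any outcome data are seen by arm.

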### 6.3.3. Economic evaluation

Economic evaluation will be implemented to compare the cost-effectiveness of CMT and UC. The primary economic endpoint will be an incremental cost-effectiveness ratio (ICER) of CMT compared with UC. ICER will be obtained by incremental cost between CMT and UC divided by incremental effectiveness between CMT and UC. Accordingly, additional cost will be calculated when 1 QALY is increased [26]. If predictions about subsequent periods are needed, cost and effectiveness after follow-up period will be extrapolated using regression models or secondary analysis such as decision modelling analysis. The treatment cost of this trial will be calculated by considering the number of treatments and their unit cost, derived from the health insurance cost and the agency cost. QOL inferred from the EQ-5D-5 L will be the primary measurement for the assessment of QALY, and the AUC method will be used [18]. If the total time horizon is more than 12 months, the cost unit will be standardized as the Korean currency (won), and a discount rate of 5% will be applied, based on the guidelines for economic assessment of the Health Insurance Review & Assessment Service. This analysis will be conducted from the societal perspective. Representative values (i.e. mean) of parameters will be used in the baseline analysis. Sensitivity analysis will be carried out in the form of probabilistic sensitivity analysis by using the distribution of all possible parameters and their representative values. In order to confirm the robustness of the analysis results, the probabilistic sensitivity analysis will be performed by setting the range of cost, effect and transition probability variable to 95% confidence interval. The utility weight and the transition probabilities will be analyzed with the triangular distribution and the cost data will be analyzed with the normal distribution for the distribution of the variable. Monte Carlo simulation will be performed 10,000 times and the mean and 95% confidence interval will be calculated. After conducting probabilistic sensitivity analysis, cost-effectiveness acceptability curve will be confirmed [27].

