## **5. Method**

### **5.1. Design**

The study design is a 2-arm parallel multicenter RCT (Kyung Hee University Hospital of Korean Medicine, Gangdong, Jaseng Hospital of Korean Medicine (Gangnam), Daejeon Jaseng Hospital of Korean Medicine, Bucheon Jaseng Hospital of Korean Medicine, Haeundae Jaseng Hospital of Korean Medicine). Study participants will receive outpatient treatment for a total of 4 weeks. After screening at the initial visit, participants who meet the inclusion/exclusion criteria will be randomly assigned to either the Chuna manual therapy group (40 participants) or the usual care group (40 participants). Treatment for temporomandibular joint (TMJ) pain disorders will be administered according to the developed clinical study protocol.

For the economic evaluation study, cost data collection and utility assessment for estimating QALY (Quality Adjusted Life Year) will be conducted. During the clinical study period, quality of life will be assessed using EQ-5D, EQ-VAS, and SF-12 measurement tools at Visits 2, 10, and 12. Various costs will be assessed using developed survey items at the first visit of each week. Additionally, a separate follow-up survey will be conducted until 6 months (Visit 12) after clinical study enrollment. The survey will be conducted through face-to-face interviews, telephone interviews, or distributed questionnaires, measuring healthcare utilization and quality of life.

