#### 5.3.2. Medical History and Medication History Investigation

The subject's medical history and medication history will be thoroughly investigated and recorded through interviews and review of past medical records. The details to be included are as follows:

- Surgical history
- Past medical history and comorbidities, treatment history for heart disease and gastrointestinal diseases
- Any adverse reactions to previous pharmacopuncture treatment and general treatments (medication, physical therapy)
- Current medical history
- Evaluation of inclusion/exclusion criteria compliance
- Other medication treatments and treatment history
- Pre-clinical study cost investigation: Investigate the treatment costs related to the disease incurred before participating in the clinical study since the onset of the disease
- Quality of life measurement: Measure the patient's quality of life before participating in the clinical study using tools such as EQ-5D-5L.

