#### Short Form-12 Health Survey (SF-12), version 2.

SF-12 will be conducted on the 1st treatment visit, prior to the treatment, a week after the last treatment, and at the 3-month and 6-month follow-ups. It contains 12 items about health-related quality of life. A higher total score reflects a better quality of life.

5-Level EuroQol-5 Dimension (EQ-5D-5 L) and EuroQol Visual Analogue Scale (EQ-VAS).

EQ-5D-5 L and EQ-VAS will be conducted on the 1st treatment visit, just before the treatment, a week after the last treatment, and at the 3-month and 6-month follow-ups. The EQ-5D-5 L evaluates health state, and the total score is indirectly calculated through a specifically developed equation. It is composed of five items (mobility, self-care, usual activities, pain, and anxiety/ depression). EQ-VAS uses a 100 mm line, which ranges from the worst health condition on the left end to the best health condition on the right end. Participants will be asked to mark the point corresponding to one's own health condition on that day.

Cost data investigation

Cost data include medical consumption, non-medical consumption and productivity loss cost of societal perspective. A questionnaire will be developed to evaluate consumption profiles, such as formal/informal medical consumption, non-medical consumption, and time consumption. While formal medical consumption refers to medical interventions and drugs, informal medical consumption refers to health food, medical instruments, etc. Non-medical consumption includes the cost of transportation, time consumption, and nursing. The Work Productivity and Activity Impairment questionnaire (WAPI) will be used for the cost of productivity impairment [24]. Medical consumption and non-medical consumption will be investigated with questionnaires which contains the cost data and the received treatment of participants and the cost data of Korean National Health Insurance will also be analyzed to calculate consumptions.

Credibility and expectancy questionnaire

The 9-point Likert scale for Credibility and Expectancy This scale is used to assess the participants' expectancy of the trial. On the 1st treatment visit, before the treatment, they will be asked how much the symptom would be reduced by the CMT and UC (1=not at all, 5=somewhat, and 9=very much).

Adverse events

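### The plan states no baseline-utility adjustment for the 6-month QALY difference behind the ICER, although it baseline-adjusts EQ-5D-5L elsewhere; adjusting would add precision at no cost

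*Protocol*

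**What the plan says.** The ICER is the primary economic endpoint. Section 6.3.3 defines it: "ICER will be obtained by incremental cost between CMT and UC divided by incremental effectiveness between CMT and UC". The effectiveness term is the QALY: "QOL inferred from the EQ-5D-5 L will be the primary measurement for the assessment of QALY, and the AUC method will be used". For the base case, "Representative values (i.e. mean) of parameters will be used in the baseline analysis". Section 1.2 of the Statistical Analysis Methods repeats all three statements. Neither section mentions baseline utility as a covariate.

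Section 6.3.2 (repeated in section 1.1 of the Statistical Analysis Methods) treats EQ-5D-5L as one of the continuous outcomes, in two ways:

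- For the change to each time point, "ANCOVA (Analysis of Covariance) will be performed with the baseline values of each variable" as covariates.
- For the total over 5 weeks and over the full 6 months, "the areas under the curve (AUC) at each time point after randomization will be calculated and compared using Student's t-test".

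On timing, section 6.2 says "EQ-5D-5 L and EQ-VAS will be conducted on the 1st treatment visit, just before the treatment, a week after the last treatment", followed by the 3-month and 6-month visits. Section 5.3.2 also asks for a measurement before the study: "Measure the patient's quality of life before participating in the clinical study using tools such as EQ-5D-5L". Baseline utility is therefore collected in every participant. Section 5.1 lists fewer times ("quality of life will be assessed using EQ-5D, EQ-VAS, and SF-12 measurement tools at Visits 2, 10, and 12"), leaving out month 3. The shift worked out below does not depend on whether month 3 is used.

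**The concern.** The 6-month area under the EQ-5D-5L utility curve is the QALY. The same scores are baseline-adjusted when they serve as a secondary clinical outcome. When they form the denominator of the primary economic result, no adjustment is stated, and the one comparison the plan names for 6-month areas is an unadjusted t-test.

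Baseline utility reaches the area by two routes. It is the first point of the curve, and it predicts the later points. With 40 per arm, a chance baseline difference passes into the incremental QALY by both. The incremental QALY over half a year is likely to be a small number, and the ICER divides by it, so modest noise in the denominator moves the ratio noticeably. The data that would remove much of this noise are already collected.

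**Working it through.** **What the plan gives.** There is no planned figure to reproduce for utility, QALY or ICER. The nearest one is the plan's own use of baseline adjustment for VAS in section 3.5: (1 − 0.3 × 0.3) × 68 = 61.9, so 62. This reproduces, and it shows that the plan already counts on the gain from adjusting for baseline.

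**Inputs from the protocol.** 40 per arm (section 3.5). EQ-5D-5L before the first treatment, one week after the last treatment (week 5), and at months 3 and 6 (section 6.2 and the timetable).

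**Assumptions, not in the documents.** Months 3 and 6 are taken as weeks 13 and 26. Utility SD is 0.15 (range 0.10 to 0.20) at every visit. The correlation r of baseline with each later utility is 0.3 to 0.5; 0.3 is the plan's figure for VAS. The sustained utility gain d from week 5 is 0.05 (also 0.10).

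**Step 1, weights.** Trapezoid weights at weeks 0, 5, 13 and 26 are 2.5, 6.5, 10.5 and 6.5 weeks, summing to 26. The baseline weight is 2.5/26 = 9.6% of the area, or w0 = 2.5/52 = 0.0481 years. Follow-up carries 23.5/52 = 0.4519 years. Without month 3 both figures are unchanged.

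**Step 2, chance imbalance.** SE of the baseline difference = SD × √(2/40) = 0.15 × 0.2236 = 0.0335.

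**Step 3, shift in the incremental QALY for a 1-SE imbalance.** The slope of QALY on baseline is w0 + r × 0.4519.

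- r = 0.3: slope 0.184; shift 0.184 × 0.0335 = 0.0062
- r = 0.5: slope 0.274; shift 0.274 × 0.0335 = 0.0092
- r = 0 (baseline score's own weight only): shift 0.0481 × 0.0335 = 0.0016

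**Step 4, against the assumed effect.** The true incremental QALY is d × 0.4519: 0.0226 for d = 0.05 and 0.0452 for d = 0.10.

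| SD | r | shift, d = 0.05 | shift, d = 0.10 |
|---|---|---|---|
| 0.10 | 0.3 | 18% | 9% |
| 0.10 | 0.5 | 27% | 14% |
| 0.15 | 0.3 | 27% | 14% |
| 0.15 | 0.5 | 41% | 20% |
| 0.20 | 0.3 | 36% | 18% |
| 0.20 | 0.5 | 54% | 27% |

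At SD 0.15 and d = 0.05, the baseline score's own weight accounts for only 0.0016/0.0226 = 7%. The rest is carry-over through correlation. If the area were taken to leave baseline out, the shift would still be r × 0.0335/0.05 = 20% to 34%.

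**Step 5, effect on the ICER.** With incremental cost held fixed, a 27% shift multiplies the ICER by 1/0.73 = 1.37 or 1/1.27 = 0.79. A 41% shift multiplies it by 1/0.59 = 1.69 or 1/1.41 = 0.71.

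**Step 6, precision.** Take SD 0.15, correlation 0.5 between all visits and d = 0.05. In 20,000 simulated trials the mean incremental QALY was 0.0227 with and without adjustment, against a true 0.0226. Its standard deviation was 0.0136 unadjusted and 0.0100 adjusted, so the variance falls by 1 − (0.0100/0.0136)² = 46%. The two estimates differed by more than a quarter of the true value in 53% of trials.

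**The case against.** The strongest reply is that section 6.3.3 never says the QALY comparison is unadjusted. The area method describes how one patient's QALY is computed, not how arms are compared. Using mean values for the base case sets point values against sampled ones, and an adjusted mean is still a mean. Covariates for a QALY regression are often left to a separate analysis plan, and the t-test sentence sits among the efficacy analyses and does not name QALYs. Section 6.3.3 also allows for decision modelling.

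Part of this stands: a reader should not infer that the documents declare the QALY unadjusted. But the position is more than silence. Section 6.3.2 names the t-test for the area of each outcome over 6 months, and EQ-5D-5L is a listed outcome. It does so next to an ANCOVA that adjusts the same scores. The protocol's own Statistical Analysis Methods repeat both statements.

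The second reply is that this is ordinary sampling error. Under randomisation both estimators are unbiased, the 1-SE shift of 0.006 to 0.009 is smaller than the unadjusted standard deviation of 0.0136, and the planned probabilistic analysis and acceptability curve are meant to show uncertainty. That is correct as to bias. It does not recover the lost precision: sampling around an unadjusted estimate leaves the result centred on it.

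**Conclusion.** The point holds as an opportunity to improve precision at no cost. No baseline-utility adjustment is stated for the quantity that drives the ICER, the only comparison named for such areas is unadjusted, and the plan already uses the better method for the same scores at single time points.

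The size is conditional on figures the documents do not give. With SD 0.15 and a sustained gain of 0.05, a 1-SE imbalance shifts the incremental QALY by about 27% to 41% for correlations of 0.3 to 0.5. A gain of 0.10 halves this, and SD 0.10 brings it to two thirds.

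Three stronger readings are not supported:

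- That the error is always a quarter or more. Several cells of the table fall below that, down to 9%.
- That the presence of baseline inside the area is the main cause. The baseline score carries only 9.6% of the area.
- That the economic result is biased or its conclusion reversed. The expected value is unaffected, and the documents give no expected costs or decision threshold against which a reversal could be judged.

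**What to change.** In section 6.3.3 and in section 1.2 of the Statistical Analysis Methods, state that the incremental QALY is estimated by regressing each participant's 6-month QALY on arm and baseline EQ-5D-5L utility. Use the adjusted difference and its confidence interval in the ICER, in the planned probabilistic sensitivity analysis and in the acceptability curve. Report unadjusted arm means as description. Say also that the t-test on areas in section 6.3.2 is not the QALY comparison.

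The cost is a sentence or two in each place. No new data, visits or participants are needed. The planned Monte Carlo approach can stay, and no bootstrap is required.
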